# Appendix A. Proteosome-Trivalent Influenza Vaccine Dose Preparation Worksheet

Date: ___________________ (dd/mm/yy)

Lot no. of proteosome-trivalent influenza vaccine: 1066

Mean Influenza hemagglutinin (HA) concentration (per strain) **____V___** μg / mL

(**V** concentration will be added by sponsor before study commencement)

Step 1. Estimate required volume of vaccine required at each dose level today:

| 15 g dose: | ______________ | X | 1.0 mL | = | ________ mL (volume A) |
| --- | --- | --- | --- | --- | --- |
|  | No. of subjects to receive 15 g dose |  |  |  |  |
|  |  |  |  |  |  |
| 30 g dose: | ______________ | X | 1.0 mL | = | ________ mL (volume B) |
|  | No. of subjects to receive 30 g dose |  |  |  |  |

Step 2. Calculate number of stock vaccine vials needed today:

| For 15 g dose: | _____ mL | | X | ( **V** / 54 ) | = | _______mL (volume C) |
| --- | --- | --- | --- | --- | --- | --- |
|  | (volume A) | |  |  |  |  |
|  |  | |  |  |  |  |
| For 30 g dose: | _____ mL | | X | ( **V** / 107 ) | = | _______mL (volume D) |
|  | (volume B) | |  |  |  |  |
|  |  | |  |  |  |  |
| Number of vials | = | ( vol. C + vol. D ) | | | ÷ | 0.9 |

Step 3. Remove requisite number of stock vaccine vials (PINK label) from refrigeration. Obtain sufficient vials of diluent/placebo (WHITE label). Diluent/placebo vials contain 10 mL of diluent; enough in one vial to yield ten (10) placebo doses or provide diluent for approximately 25 active doses. Obtain vaccine dilution vials.

Step 4. Prepare a nasal spray pump reservoir vial labeled with the ID no. of each subject to be dosed.

Step 5. Label vaccine dilution vials (vials and labels provided by sponsor) for the active and placebo test articles.

Initial this page: ___________

Vaccine Dose Preparation Worksheet, page 2.

Step 6. Swirl stock vaccine vial(s) before withdrawing vaccine to ensure complete mixing. Prepare the final vaccine dilution and placebo by adding the following volumes to the vaccine dilution vial(s), using the calculations performed on page 1 of this worksheet.

|  |  | Stock Vaccine |  | Placebo/Diluent |
| --- | --- | --- | --- | --- |
|  |  |  |  |  |
| 15 g active |  | _____ mL | + | ______ mL |
|  |  | Volume C |  | (Volume A – Volume C) |
|  |  |  |  |  |
| 30 g active |  | _____ mL | + | ______ mL |
|  |  | Volume D |  | (Volume B – Volume D) |
|  |  |  |  |  |
| Placebo |  | 0 | + | ______ mL |
|  |  |  |  | (number of placebo subjects X 1.0 mL) |

Swirl each dilution vial gently to ensure complete mixing.

Step 7. Referring to the treatment assignment list, determine the appropriate test article for each subject and place 0.9 mL of active vaccine dilution or placebo in the reservoir vial of the nasal spray device. Assemble the nasal spray pump onto the reservoir vial. Enter the required information for the subject in question into the Dose Preparation Log.

Step 8. Remove the nosepiece cover and then the safety collar from the nasal spray pump. Hold the assembled pump upright and fully depress the actuator three (3) times to prime the pump. Replace the safety collar, then the nosepiece cover. Deliver the pump to the clinic for test article administration.

Step 9. All stock vaccine and placebo vials and all vaccine dilution vials should be recapped and retained in a separate, secure location (which may be at room temperature) for return to the sponsor. NO VIAL THAT HAS BEEN PREVIOUSLY ENTERED SHOULD BE RE-USED.

Sign and date this form: ______________________________ _____________

Signature Date

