In humans, ID Biomedical has now carried out a total of six (6) clinical trials of proteosome-influenza vaccines given by the intranasal route (37 – 40). The first two (2) of these studies evaluated a monovalent prototype vaccine; the subsequent four (4) have utilized trivalent preparations including influenza A/H1N1 and A/H3N2 subtype antigens and influenza B antigens. These studies have evaluated a total of 387 healthy adult subjects of both genders and between the ages of 18 and 50; of these 304 have received active proteosome-influenza vaccine products and 83 have received either a saline placebo or another comparator. In the monovalent vaccine trials, intranasal doses containing between 7.5 and 45 μg of influenza virus hemagglutinin (HA) formulated with an approximate four-fold excess of proteosome proteins have been studied. In trivalent vaccine trials, doses containing between 15 and 45 μg of *each* of the three influenza virus HAs, also with an approximate four-fold excess of proteosome proteins, have been evaluated. Single-dose regimens and regimens providing two doses at a 14-day interval have been tested. Safety and immunogenicity results have been consistent between the monovalent and trivalent programs.

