## 5.1 Immunization Phase:

FluINsure™ will be delivered as one of three different treatment regimens as detailed below in section 5.1.1. In addition, approximately one of every four subjects will receive a placebo control treatment regimen comprising two sequential doses of buffered saline placebo.

The study will enroll up to 112 healthy adult subjects selected for susceptibility to A/Panama/2007/99 into the immunization component.

Healthy normal subjects of both genders and 18 to 50 y.o. will be invited to give informed consent for preliminary screening phlebotomy, and then have a serum specimen obtained for baseline A/Panama/2007/99 HAI antibody testing. Screened subjects with serum reciprocal HAI titers ≤ 10 will be invited to return for a detailed explanation of the clinical trial and asked to give informed consent for participation in the trial itself. Consenting subjects will then undergo an assessment of their medical history, physical examination, ECG, and selected clinical laboratory tests to ensure eligibility according to the protocol. A nasal wash sample for measurement of secretory IgA (nasal sIgA) specific for the vaccine virus strains will be obtained during screening.

5.1.1 Treatments:

Eligible subjects will be randomized, using a gender-specific randomisation list prepared by the Sponsor, to one of four treatment groups in a ratio of approximately 1:1:1:1. The treatment groups will receive:

Treatment Group A) Two intranasal spray doses, each dose containing 15 μg of each of three hemagglutinins (HA) formulated with proteosomes. The first dose will be given on day 0 and the second given after a 14-day interval.

Treatment Group B) Two intranasal spray doses, the first containing 30 μg of each of three hemagglutinins (HA) formulated with proteosomes, and the second containing buffered saline (placebo). The first dose will be given on day 0 and the second given after a 14-day interval.

Treatment Group C) Two intranasal spray doses, each containing 30 μg of each of three hemagglutinins (HA) formulated with proteosomes. The first dose will be given on day 0 and the second given after a 14-day interval.

Treatment Group D) Two intranasal spray doses of buffered saline. The first dose will be given on day 0 and the second given after a 14-day interval.

All dose volumes will be 0.28 mL (as 0.14 mL per nostril). Each treatment group will include approximately 28 subjects.

5.1.2 Safety and Tolerability Evaluation:

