# 6.0 Investigational Supplies:

## 6.1 Study Drugs:

Proteosome-trivalent influenza vaccine (*PINK LABEL*): a sterile, colorless to yellowish opalescent liquid containing 150  30 g / mL of hemagglutinin (HA) from each of A/New Caledonia /20/99 (H1N1), A/Panama/2007/99 (H3N2), and B/Shangdong/7/97 viruses in 10 mM Na/K phosphate-buffered isotonic saline, pH 7.4, with 0.01% thimerosal. Non-hemagglutinin viral proteins are also present. The virus components are formulated with outer membrane proteins (OMP) of *Neisseria meningitidis* strain 8047, at an initial ratio of OMPs to HA of 4:1. The overall total protein to hemagglutinin ratio in the final vaccine product is 2.5 – 5:1 (varies slightly with viral strain and non-hemagglutinin protein losses during the complexing process). The vaccine also contains trace amounts of egg proteins. The vaccine is delivered in 3 mL borosilicate glass vials containing **an 0.9** mL fill.

Phosphate-buffered normal saline diluent/placebo (*WHITE LABEL*): a sterile, colorless liquid comprising 10 mM Na/K phosphate-buffered isotonic saline, pH 7.4, with 0.01% thimerosal, delivered in 20 mL borosilicate vials with a 10 mL fill.

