### 6.4.2 Preparation of Individual Test Article Doses:

A test article dose will be prepared for each subject to be dosed by placing a total of 0.9 mL of appropriately diluted active vaccine or placebo/diluent, as dictated by the treatment group assignment, into the vial of the previously labeled metered dose pump, after which the actuator and nose piece will be assembled to the pump. Since the target concentrations of each of the three HA species in the vaccine are approximately equal, dosing and dilution will be based on the mean HA concentration in the trivalent (i.e., the average of the concentrations of the three different HAs). Detailed instructions and dose preparation worksheets are provided as Appendix A. After assembly of the pump, the pharmacist will hold the metered dose pump upright, gently swirl once again, remove the nosepiece and then the safety collar, and firmly and fully depress the actuator three (3) times to prime the pump. The collar and then the nosepiece cover will be replaced after priming, and the labeled, filled, and primed pump will be delivered to the clinic.

After test article preparation is completed for a given day, any opened stock vaccine and/or saline placebo vials will be restoppered and retained for retrieval by an ID Biomedical representative.

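### The dose-preparation worksheet inverts the dilution ratio (V/54 and V/107), so the diluent volume comes out negative and neither the 15 µg nor the 30 µg dose can be made from it

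*Protocol*

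**What the plan says.** Section 5.1.1 sets two dose levels, 15 µg and 30 µg of each HA, and one delivered volume: "All dose volumes will be 0.28 mL (as 0.14 mL per nostril"). Section 6.1 describes the stock as "a sterile, colorless to yellowish opalescent liquid containing 150" µg/mL of HA per strain, with a tolerance of 30. Section 6.4.2 states that "dosing and dilution will be based on the mean HA concentration in the trivalent" and sends the pharmacist to Appendix A for the instructions.

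Appendix A calls the stock's mean HA concentration V. It is left blank, with a note that the "concentration will be added by sponsor before study commencement". The calculation then runs as follows.

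- Step 1: volume A (15 µg) and volume B (30 µg) are the number of subjects × 1.0 mL.
- Step 2 ("Step 2. Calculate number of stock vaccine vials needed today"): stock volume C = A × (V/54) and D = B × (V/107). The vial count is (C + D)/0.9.
- Step 3: a 10 mL diluent vial is "enough in one vial to yield ten (10) placebo doses or provide diluent for approximately 25 active doses".
- Step 6: mix stock C with diluent ("Volume A – Volume C") for the 15 µg dose, and stock D with diluent B − D for the 30 µg dose.

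**The concern.** Diluting a stock to a weaker target takes a stock volume smaller than the final volume, so the multiplier must be below 1. With a stock near 150 µg/mL, V/54 and V/107 are both above 1. The worksheet therefore asks for more stock than the finished volume and leaves a negative amount of diluent to add.

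Section 1.0 gives as one of the study's aims to learn whether two doses at 15 µg protect, alongside the 30 µg regimens. That comparison exists only if the two dilutions are made correctly. A pharmacist who follows the page reaches an impossible volume and has to improvise, and the repair could differ between dosing days. One possible response is to use undiluted stock for every active dose. Groups A and C would then receive the same regimen, at an HA content matching neither stated dose.

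**Working it through.** **Inputs**

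- Doses of 15 and 30 µg per HA in 0.28 mL (5.1.1).
- Stock V = 150 ± 30 µg/mL, that is 120 to 180 (6.1). The ± sign is lost in the text available, so reading the 30 as a tolerance is an assumption. V for lot 1066 is blank.
- Factors V/54 and V/107, 1.0 mL prepared per subject, 0.9 mL per stock vial (Appendix A).
- 28 subjects per group (5.1.1). Day 0 has 28 doses at 15 µg (group A) and 56 at 30 µg (groups B and C). Day 14 has 28 and 28, because group B then receives placebo.

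**Step 1. What 54 and 107 are.** Target concentration = dose / volume: 15/0.28 = 53.6 and 30/0.28 = 107.1 µg/mL. Rounded, these are the worksheet's constants.

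**Step 2. The ratio needed.** HA is conserved, so stock volume × V = final volume × target. Stock volume = final volume × target/V, which means 54/V and 107/V. The printed factors are the reciprocals.

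**Step 3. Both versions, per 1.0 mL of final product (mL)**

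| V (µg/mL) | Dose | Stock, as printed | Diluent, as printed | Stock, target/V | Diluent, target/V |
|---|---|---|---|---|---|
| 120 | 15 µg | 2.22 | −1.22 | 0.45 | 0.55 |
| 120 | 30 µg | 1.12 | −0.12 | 0.89 | 0.11 |
| 150 | 15 µg | 2.78 | −1.78 | 0.36 | 0.64 |
| 150 | 30 µg | 1.40 | −0.40 | 0.713 | 0.287 |
| 180 | 15 µg | 3.33 | −2.33 | 0.30 | 0.70 |
| 180 | 30 µg | 1.68 | −0.68 | 0.59 | 0.41 |

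As printed, diluent is negative in every row. With target/V it is positive in every row, and the delivered doses are 54 × 0.28 = 15.1 µg and 107 × 0.28 = 30.0 µg.

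**Step 4. The worksheet's own figure of about 25 doses.** The printed ratios give no positive diluent volume, so they cannot produce it. With target/V at V = 150 and the day 0 mix, mean diluent = (28 × 0.640 + 56 × 0.287)/84 = 0.404 mL per dose, and 10/0.404 = 24.7 doses. The closeness depends on those choices: the day 14 mix at V = 150 gives 21.6, and the day 0 mix gives 39.1 at V = 120 and 19.9 at V = 180.

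**Step 5. Vial count, if all day 0 doses are taken together at V = 150.** As printed: (28 × 2.778 + 56 × 1.402)/0.9 = 173.6, so 174 vials. With target/V: (28 × 0.360 + 56 × 0.713)/0.9 = 55.6, so 56 vials.

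**Step 6. If undiluted stock were used.** 0.28 × V = 33.6, 42.0 and 50.4 µg per HA at V = 120, 150 and 180. At V = 150 that is 42/15 = 2.8 times and 42/30 = 1.4 times the stated doses. Section 1.0 reports that earlier trivalent trials used "doses containing between 15 and 45 μg of *each* of the three influenza virus HAs". Undiluted stock would pass that maximum once V exceeds 45/0.28 = 161 µg/mL.

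**The case against.** The strongest reply is that the error exposes itself. A negative volume cannot be measured out, Step 6 requires a diluent volume for each dose level, and the sponsor has to handle this same page to enter V. The correct ratio can also be rebuilt from the doses and volume in 5.1.1, the stock strength in 6.1 and the Step 3 remark that active doses need diluent. Unnoticed misdosing is therefore unlikely, and undiluted dosing is one possible outcome that the protocol nowhere prescribes. Even then group B would still receive a single active dose, so the contrast between one and two doses would survive. The volumes used would also be on record, because the worksheet is initialled and signed, a preparation log is kept and vials are retained.

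All of that stands, and it limits the likely harm. It leaves the formula wrong. No other section supplies a dilution rule, and a record of the volumes used does not make an improvised rule correct or uniform across dosing days. Faulty PDF reading is not a plausible explanation, since the factor reads cleanly in both rows and a lost symbol would not invert two fractions. The near match to 25 doses is only supporting evidence, but any positive diluent volume at all contradicts the printed ratio.

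**Conclusion.** Wrong as written, and to be corrected before the first dose. Both dilution ratios are inverted, and at every stock strength within 120 to 180 µg/mL the worksheet gives negative diluent for both dose levels. The conclusion does not depend on the blank V or on reading the 30 as a tolerance: any V above 107 µg/mL makes both diluent volumes negative, and a stock below 107 could not be diluted to the 30 µg target at all. The overdose factors of 2.8 and 1.4 rest on V = 150 and on undiluted stock being used, so they show what could happen and do not predict it. The vial counts of 174 and 56 assume V = 150 and all day 0 doses taken together.

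**What to change.** In Appendix A, Step 2, replace V/54 with 54/V and V/107 with 107/V. The vial count and the Step 6 diluent volumes then follow without further change. Once V is known for lot 1066, add a worked example (at V = 150: 0.36 mL stock + 0.64 mL diluent for 15 µg, and 0.713 mL + 0.287 mL for 30 µg, per 1.0 mL). Add a check line for the pharmacist to initial: C below A, D below B, both diluent volumes above zero. The cost is one corrected appendix page reissued to the pharmacist before dosing. Design, sample size and analysis do not change.

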# Appendix B. Table B.1

IDB-13005 Time and Events Schedule: Immunization Phase

| **Immunization Phase Day** | **-150 to**  **-7** | **-90 to - 5** | **0** | **1** | **2** | **3** | **4** | **5** | **6** | **7** | **14** | **15** | **16** | **17** | **18** | **19** | **20** | **21** | **28** |
| --- | --- | --- | --- | --- | --- | --- | --- | --- | --- | --- | --- | --- | --- | --- | --- | --- | --- | --- | --- |
| **Screening consent** | **x** |  |  |  |  |  |  |  |  |  |  |  |  |  |  |  |  |  |  |
| **Medical history** | **x** |  | **x** |  |  |  |  |  |  |  | **x** |  |  |  |  |  |  |  |  |
| **A/Panama HAI titer** | **x** |  |  |  |  |  |  |  |  |  |  |  |  |  |  |  |  |  |  |
| **Clinical Trial Consent** |  | **x** |  |  |  |  |  |  |  |  |  |  |  |  |  |  |  |  |  |
| **ECG** |  | **x** |  |  |  |  |  |  |  |  |  |  |  |  |  |  |  |  |  |
| **Clinical hematology/chem.** |  | **x** |  |  |  |  |  |  |  |  |  |  |  |  |  |  |  |  | **x** |
| **Urinalysis** |  | **x** |  |  |  |  |  |  |  |  |  |  |  |  |  |  |  |  | **x** |
| **HIV serology** |  | **x** |  |  |  |  |  |  |  |  |  |  |  |  |  |  |  |  |  |
| **Drugs of abuse screening** |  | **x** |  |  |  |  |  |  |  |  |  |  |  |  |  |  |  |  |  |
| **Nasal wash for spec. IgA** |  | **x** |  |  |  |  |  |  |  |  |  |  |  |  |  |  |  |  | **x** |
| **Serum for HAI antibody** |  |  | **x** |  |  |  |  |  |  |  |  |  |  |  |  |  |  |  | **x** |
| **Whole blood for cytokine studies** |  |  | **x** |  |  |  |  |  |  |  |  |  |  |  |  |  |  |  | **x** |
| **-HCG (females)** |  |  | **x** |  |  |  |  |  |  |  | **x** |  |  |  |  |  |  |  |  |
| **Complete physical examination** |  | **x** |  |  |  |  |  |  |  |  |  |  |  |  |  |  |  |  |  |
| **Vital signs** |  | **x** | **x** |  |  |  |  |  |  | **x** | **x** |  |  |  |  |  |  | **x** |  |
| **Brief directed examination** |  |  | **x** | **c** | **c** | **c** | **c** | **c** | **c** | **x** | **x** | **c** | **c** | **c** | **c** | **c** | **c** | **x** |  |
| **Test article dose** |  |  | **X** |  |  |  |  |  |  |  | **X** |  |  |  |  |  |  |  |  |
| **Immed. complaint quest.** |  |  | **x** |  |  |  |  |  |  |  | **x** |  |  |  |  |  |  |  |  |
| **Memory Aid** |  |  | **x** | **x** | **x** | **x** | **x** | **x** | **x** |  | **x** | **x** | **x** | **x** | **x** | **x** | **x** |  |  |
| **AEs/Con. meds.** |  |  | **x** |  |  |  |  |  |  | **x** | **x** |  |  |  |  |  |  | **x** | **x** |

**x** = scheduled event; **c** = contingent event, performed only if required by reactogenicity symptoms

**Note: Study days following day 0 represent the nominal study schedule. Acceptable variability at each time point is indicated in protocol text.**

# Appendix B. Table B.2

IDB-13005 Time and Events Schedule: Challenge Phase

| ***Day Relative to First Treatment*** | ***39*** | ***40*** | ***41*** | ***42*** | ***43*** | ***44*** | ***45*** | ***46*** | ***47*** | ***48*** | ***49*** | ***50*** | ***51*** | ***60 - 70*** |
| --- | --- | --- | --- | --- | --- | --- | --- | --- | --- | --- | --- | --- | --- | --- |
| **Challenge Phase Day** | **0** | **1** | **2** | **3** | **4** | **5** | **6** | **7** | **8** | **9** | **10** | **11** | **12** | **20 - 30** |
| **Admit to quarantine** | **x** |  |  |  |  |  |  |  |  |  |  |  |  |  |
| **Interval medical history** | **x** |  |  |  |  |  |  |  |  |  |  |  |  |  |
| **ECG** | **x** |  |  |  |  |  |  |  | **x** | |  |  |  | **c** |
| **Nasal wash for spec. IgA** | **x** |  |  |  |  |  |  |  |  |  |  |  |  | **x** |
| **Serum for HAI antibody** | **x** |  |  |  |  |  |  |  |  |  |  |  |  | **x** |
| **Complete Physical exam (with vital signs)** | **x** |  |  |  |  |  |  |  | **x** | | **c** |  |  | **x** |
| **-HCG (females)** |  |  | **x** |  |  |  |  |  |  |  |  |  |  |  |
| ***Challenge inoculum*** |  |  | ***X*** |  |  |  |  |  |  |  |  |  |  |  |
| **Temperature only, q.i.d.** |  | **x** | **x** | **x** | **x** | **x** | **x** | **x** | **x** | **x** |  |  |  | **x** |
| **Symptom Diary Card** | **x** | **x** | **x** | **x** | **x** | **x** | **x** | **x** | **x** | **x** |  |  |  |  |
| **24 hour tissue counts** |  | **x** | **x** | **x** | **x** | **x** | **x** | **x** | **x** | **x** |  |  |  |  |
| **Directed physical examination, BP and pulse** |  | **x** | **x** | **x** | **x** | **x** | **x** | **x** | **x** | **x** |  |  |  |  |
| **Throat swab for detection and / or quantitation of influenza virus** |  |  | **x** | **x** | **x** | **x** | **x** | **x** | **x** | **x** |  |  |  |  |
| **Nasal wash for detection and / or quantitation of influenza virus** |  |  |  | **x** | **x** | **x** | **x** | **x** | **x** | **x** |  |  |  |  |
| **Oseltamivir treatment** |  |  |  |  |  |  |  |  | **x** | **x** | **x** | **x** | **x** |  |
| **Discharge from isolation** |  |  |  |  |  |  |  |  |  | **x** | **c** |  |  |  |
| **AEs/Con. meds.** | **x** | **x** | **x** | **x** | **x** | **x** | **x** | **x** | **x** | **x** |  |  |  | **x** |

**x** = scheduled event; **c** = contingent event, performed only if required by illness or antecedent abnormal ECG

**Note: Study days represent the nominal study schedule. Acceptable variability at each time point is indicated in protocol text.**

# Appendix C. Brief Examination Worksheet (Post-Immunization)

Study IDB-13005 Subject ID:_____________ Date:________ Observer’s Initials ______________

Study Day: 0 7 ± 1 14 21±1

For each category of observation, place an “X” in the box most descriptive of the observations made.

|  | **Grade 0** | **Grade 1** | **Grade 2** | **Grade 3** |
| --- | --- | --- | --- | --- |
| **Nasal mucosal inflammation** | None | Erythema or edema | Erythema and edema | Ulceration |
| **Nasal discharge** | None | Clear, serous, scant | Purulent | Bloody  purulent |
| **Pharyngeal inflammation** | None | Mild or patchy erythema | Severe erythema | Purulent exudate |
| **Sinusitis** | None | **NO GRADE 1** | Mild tenderness | Severe tenderness or overlying erythema |
| **Cervical/ post-auricular nodes** | None | Minimal enlargement, firm, nontender | Moderate enlargement, firm, slight tenderness | V. enlarged, soft/fluctuant, severe tenderness |
| Otic inflammation | None | Dull tympanic membrane | Injected tympanic membrane | Retracted or bulging tympanic membrane, fluid |

# Appendix D. Prototype Memory Aid Page

**SID #:** __________  **Initials: ___ ____ ____**

|  | Study Day X | | | | | | | |  | | | | | | | | | | | | | | | | |  |
| --- | --- | --- | --- | --- | --- | --- | --- | --- | --- | --- | --- | --- | --- | --- | --- | --- | --- | --- | --- | --- | --- | --- | --- | --- | --- | --- |
| Today’s date (day/month/year) |  | |  | | 200__ | | | |  | |  | | | |  | | | |  | | | | | | | |
| Evening oral temperature: | C | | | | | | | |  | | | | | | | | | |  | | | | | | | |
|  | Grade (Mark the appropriate box) | | | | | | | |  | | | | | | | | | | | | | | | | |  |
|  | **0** | **1** | | **2** | | **3** | | |  | | | |  | | | |  | | | |  | | | | |  |
| Did you feel tired or have less energy than usual? |  |  | |  | |  | | |  | | | |  | | | |  | | | |  | | | | |  |
| Was your appetite poor? |  |  | |  | |  | | |  | | | |  | | | |  | | | |  | | | | |  |
| Did you have a headache? |  |  | |  | |  | | |  | | | |  | | | |  | | | |  | | | | |  |
| Did you have muscle or joint aches? |  |  | |  | |  | | |  | | | |  | | | |  | | | |  | | | | |  |
| Did you have a runny nose? |  |  | |  | |  | | |  | | | |  | | | |  | | | |  | | | | |  |
| Did you have a stuffy nose? |  |  | |  | |  | | |  | | | |  | | | |  | | | |  | | | | |  |
| Did your nose burn or itch? |  |  | |  | |  | | |  | | | | | | | | | | | | | | | | |  |
| Did you have bleeding from your nose? |  |  | |  | |  | | |  | | |  | |  | |  | |  | |  | | |  | |  | |
| Did you have red or puffy eyes? |  |  | |  | |  | | |  | | |  | |  | |  | |  | |  | | |  | |  | |
| Did you have any sneezing? |  |  | |  | |  | | |  | | |  | | | | | | | | | |  | | | | |
| Did you have a sore throat? |  |  | |  | |  | | |  | | |  | | | | | | | | | |  | | | | |
| Did you have a cough? |  |  | |  | |  | | |  | | |  | | | | | | | | | |  | | | | |
| Did you have shortness of breath or wheezing? |  |  | |  | |  | | |  | | | |  | | | |  | | | |  | | |  | | |
|  |  | | | | | | |  | |  | | |  | | | | | |  | | | | | | | |
| Did you take any medications on this day? | No | | | | | | Yes | | | | | | | | | | | |  | | | | | | | |
| *If yes,* list medication(s) below: | | | | | | | | | | | | | | | | | | |  | | | | | | | |
|  | | | | | | | | | | | | | | | | | | |  | | | | | | | |
|  | | | | | | | | | | | | | | | | | | |  | | | | | | | |
|  | | | | | | | | | | | | | | | | | | |  | | | | | | | |
|  | | | | | | | | | | | | | | | | | | |  | | | | | | | |
| Grade Definitions:  *Grade 0* = Not at all.  *Grade 1* = I noticed it, but it didn’t really interfere with any of my usual activities significantly.  *Grade 2* = I had it, and it was bad enough that I couldn’t do a significant part of my usual activities.  *Grade 3* = I had it, and it was bad enough that I was not able to do most of my usual activities, or I had to get prescription medicine from a doctor. | | | | | | | | | | | | | | | | | | |  | | | | | | | |

